### Trial design and setting

The Sparky Samba trial is a parallel-group feasibility RCT of the Sparky Samba intervention compared with an activities-as-usual control group. We will recruit 60 PwP to be randomised 1:1 to the intervention or activities as usual for a period of 12 weeks. The recruitment target of 60 has been selected in line with guidance for sample sizes in feasibility studies.^18^ This sample size will allow estimation of recruitment, retention, adherence and data completeness rates with a 95% binomial CI of no more than plus or minus 13 percentage points irrespective of the point estimate. The trial is not powered for hypothesis tests to detect effects in the clinical outcome measures.

The trial will be conducted in three secondary care (National Health Service (NHS)) sites across Wales, UK, with the Sparky Samba intervention delivered at three local community sites identified and supported by the Sparky Samba group. The clinical sites have been selected due to their co-location with the Sparky Samba groups to facilitate attendance of participants at the Samba groups.

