### Outcomes

The primary outcome for this trial is feasibility as defined by participant recruitment, retention, intervention adherence and data completeness according to pre-specified criteria. Thresholds for the feasibility criteria are detailed in table 1.

**Table 1 T1:** Measures of feasibility and pre-defined criteria for success used to determine the primary outcome

Variable	Progression criteria		
	Red	Amber	Green
Recruitment			
% of people approached who are willing to participate (100*(number consented/number approached)%)	<5%	5–19.9%	≥20%
Number recruited	<25	25-44	45-60
Retention			
% of participants attending the primary 12-week endpoint assessment (100*(number attending/number consented)%)	<50%	50–89.9%	≥90%
Adherence			
% of participants adherent to the intervention (attending ≥8 sessions) (100*(number adherent/number consented)%)	<50%	50–79.9%	≥80%
Data completeness			
% of participants completing at least 90% of baseline measures (100*(number completing ≥90%/number consented)%)	<70%	70–94.9%	≥95%
% of participants completing at least 90% of follow-up measures (100*(number completing ≥90%/number consented)%)	<50%	50–74.9%	≥75%

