Secondary outcomes to be collected include those measuring motor function, cognition, well-being, participation and self-efficacy. Individual outcomes are detailed in table 2. Functional outcomes are assessed within the hospital setting at baseline and again at 12 weeks following the intervention delivery period (table 3). Site staff delegated to perform the functional assessments will receive training from the central trial team at the site initiation visit, with an accompanying assessment manual and ad-hoc support from the trial team and clinically qualified members of the TMG. Demographic data (age, sex, ethnicity and educational level) and current medications will also be collected at baseline to provide cohort descriptives. Intervention adherence will be recorded weekly through self-report by the participant and by report from the Sparky Samba group leader/local organiser. At the end of the 12-week trial period, participants in the control group will be asked to detail the activities they have participated in for the previous 12 weeks. As retention is part of the feasibility outcome and the follow-up period is just 12 weeks long, we will not be enacting any specific strategies to boost retention beyond supporting travel to intervention sessions and enabling the flexibility described for completing outcome assessments.

**Table 2 T2:** Secondary outcomes collected in the Sparky Samba trial

Construct	Measure
Motor	Unified Parkinson’s Disease Rating Scale (UPDRS) section III(^22^): we will use this to assess global motor function in participants.
	Freezing of Gait (FoG)(^28^): this is a patient self-report measure designed to assess the severity of gait freezing in PwP.
	Dresden Falls Questionnaire (DREFAQ)(^29^): this is a patient self-report questionnaire designed to assess the risk and severity of falls, a common symptom in PwP.
	Mini-Balance Evaluation Systems Test (Mini-BES Test)(^30^): in this assessment participants are assessed across dynamic balance, functional ability and gait.
	Physical Activity Scale for the Elderly (PASE) (^31^): this questionnaire is designed to capture the level of physical activity across a range of usual activities over the past 7 days.
Cognition	Montreal Cognitive Assessment (MoCA)(^32^): we will use the truncated on-line version of the MoCA, known as XpressO, to assess cognitive function in participants. This is well validated for assessing cognitive function in PwP.

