### Analysis

Key demographic data will be summarised using descriptive statistics. For feasibility outcomes, recruitment will be assessed as the percentage of people approached who provide consent to participate in the trial; retention as the percentage of participants recruited who attend the 12-week follow-up assessment (primary endpoint); adherence as the percentage of participants adherent to the intervention (where intervention adherence is defined as attending ≥8 of 12 sessions) and data completeness as the percentage of participants completing ≥90% of baseline and follow-up measures, respectively (table 1). Feasibility criteria will be assessed according to a traffic light system with green (proceed to full effectiveness RCT) if all criteria listed in table 1 are in the green zone; amber (requiring adjustment before proceeding to full RCT) if all criteria are either in the amber or green zone; and red (do not progress to full RCT unless major changes are implemented) if at least one criterion is in the red zone. For secondary outcome measures, we will calculate descriptive summaries by arm, such as mean and standard deviation (or median and IQR, in case of a distinctly non-normal distribution) and 95% CIs of participants’ changes from baseline to 12-week follow-up. This will provide estimates of effect size and variability of drumming-induced changes for use in power calculations for a future large-scale RCT. No sub-group, sensitivity or interim analyses will be conducted. Reporting of results will follow the Consolidated Standards of Reporting Trials (CONSORT) guideline extension for pilot and feasibility studies.^26^ The statistical analysis plan will be available via ISRCTN (*ISRCTN11861663*).

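### The article names the observed effect size as an input to the full trial's power calculation; with about 27 per arm it is too imprecise for that use and could mis-size the full trial in either direction

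*Protocol article*

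**What the plan says.** The Trial design and setting section plans 60 participants: "We will recruit 60 PwP to be randomised 1:1 to the intervention or activities as usual for a period of 12 weeks". It justifies that number by the precision of the feasibility rates, "with a 95% binomial CI of no more than plus or minus 13 percentage points irrespective of the point estimate", and then states: "The trial is not powered for hypothesis tests to detect effects in the clinical outcome measures".

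The Outcomes section makes feasibility the only primary outcome. Table 2 lists nine secondary measures without ranking: UPDRS III, FoG, DREFAQ, Mini-BES Test, PASE, MoCA (XpressO), PDQ-8, OxPAQ and the Lorig scale. None is named as candidate primary outcome for the full trial.

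The Analysis section plans summaries by arm with 95% CIs for change from baseline to 12 weeks, and gives their purpose: "This will provide estimates of effect size and variability of drumming-induced changes for use in power calculations for a future large-scale RCT".

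**The concern.** The last sentence gives two products of this trial the same role in sizing the next one. They are not equally well estimated. An SD from a little over 50 participants is known closely enough to plan with. A treatment effect from the same participants is not, and the sample size varies with the inverse square of the effect, so an error in it is magnified.

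This is a stated use of the data, not a detail left to the analysis plan. At stake is the size of the full effectiveness trial, which this study exists to prepare. An overestimate makes that trial too small, an underestimate makes it needlessly large, and an estimate of the wrong sign could stop it.

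**Working it through.** **The article's own figure.** For a rate with all 60 as denominator, the largest half-width is 1.96 × √(0.25/60) = 12.65 percentage points (exact binomial limits: 13.19). This agrees with the stated 13. It covers feasibility rates only; the article gives no precision for any clinical effect.

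**Inputs.**
- 30 per arm: 60 randomised 1:1 (Trial design and setting).
- 90% retention: the green threshold in Table 1. So 30 × 0.90 = 27 per arm. The article does not state 27.
- At the bottom of the green recruitment zone, 45 × 0.90 / 2 ≈ 20 per arm.
- Assumed, because the article gives none: true standardised difference d = 0.30, two-sided 5%, target power 90% or 80%.
- The calculation takes a between-arm difference. The article describes only changes by arm, but a between-arm difference can be derived from them, and it is the quantity a power calculation needs.

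**Step 1: precision of the effect.** SE(d) ≈ √(2/n) = √(2/27) = 0.272. The 95% half-width is 1.96 × 0.272 = 0.53 SD. A true d of 0.30 would be observed between −0.23 and 0.83 in 95% of repetitions. By contrast, the pooled SD on 52 degrees of freedom has 95% limits of 0.84 and 1.24 times its estimate.

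**Step 2: sample size implied.** Per arm, n = 2 × ((1.96 + 1.2816)/d)² at 90% power.
- True d = 0.30: 234.
- Lower quartile of estimates, 0.30 − 0.6745 × 0.272 = 0.116: about 1,550 (1,535 if the quartile is rounded to 0.117).
- Upper quartile, 0.30 + 0.6745 × 0.272 = 0.484: 90.
- Upper 95% point, 0.83: about 30.

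**Step 3: true power of the resulting trial.** If the observed value x is the target, true power is Φ(0.30 × A/x − 1.96), where A = 1.96 + 1.2816 for 90% target power or 1.96 + 0.8416 for 80%.
- 90% target: power is below 80% when x > 0.30 × 3.2416/2.8016 = 0.347. P(x > 0.347) = 0.431 and P(x > 0) = 0.865, so among positive estimates 0.431/0.865 = 50%.
- 80% target: the cut is x > 0.30, so 0.500/0.865 = 58%.
- The other direction: x < 0.30/√2 = 0.212 more than doubles the required n. P(0 < x < 0.212) = 0.238, so 0.238/0.865 = 28% of positive estimates. A further 13.5% of all estimates are negative.

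Share of positive estimates giving true power below 80% / below 50%, with true d = 0.30:

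| Analysed per arm | 95% half-width | 90% target | 80% target |
|---|---|---|---|
| 20 | 0.62 | 53% / 32% | 60% / 41% |
| 27 | 0.53 | 50% / 27% | 58% / 37% |
| 30 | 0.51 | 49% / 25% | 57% / 35% |

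With 27 per arm and an 80% target, the share below 80% power is 65% if true d = 0.20 and 51% if true d = 0.50.

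**Step 4: conditional case only.** Suppose the largest of nine observed effects were chosen, all with true d = 0.30. Simulation with 27 per arm and an 80% target gives a mean selected effect of 0.70 (no correlation between outcomes) to 0.52 (correlation 0.7). Median true power is then 23% to 36%, and power falls below 80% in over 99% to 83% of cases.

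**The case against.** The strongest reply is that the sentence commits the team to little. It offers the estimates for use in power calculations; it does not say that the point estimate will be the target difference, nor does it exclude a minimally important difference. The planned 95% CIs would show the imprecision, and the article openly disclaims power for these outcomes. All of that is fair, and it is why the result is stated as a risk. It does not remove the point, because effect size is still named as an input.

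Three stronger readings are tempting and are not supported:
- **That the outcome with the largest effect will be chosen.** A reader might infer this from nine unranked measures and no candidate primary outcome. The article says nothing of the kind, and choosing the full trial's primary outcome is normally a later decision. The Public and Patient involvement section shows patients helping to select outcome measures, which is some evidence against a purely data-driven choice. Step 4 is therefore a conditional risk.
- **That the full trial would be underpowered.** Noise alone does not make this certain. At a 90% target, half of positive estimates still give at least 80% power, and many oversize the trial.
- **That the decision to progress is compromised.** The traffic-light rule uses only recruitment, retention, adherence and completeness.

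The variability half of the sentence is sound and should stay. Whether change within an arm can be called drumming-induced is a separate question; the imprecision remains even with a proper between-arm contrast.

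**Conclusion.** The concern holds in limited form. Naming the observed effect size as a power input is poor practice in a trial of this size. The estimate carries about ±0.53 SD, wider than the assumed true effect of 0.30. Used as the target difference, it could produce a full trial several times too large or less than half the size needed (90 against 234 per arm at the upper quartile), with true power below 80% in about 50% to 58% of positive-estimate cases.

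These figures rest on 27 analysed per arm, true d = 0.30, a two-sided 5% test, and use of the observed effect as the target. Analysing 20 or 30 per arm moves them by only a few points. The feasibility conclusions and the progression rule are unaffected. The change is worth making because it is nearly free and protects the design of the next trial.

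**What to change.** In the Analysis section, remove effect size as an input to the future power calculation and state instead that:
- the trial will supply the SD of each outcome with an upper confidence limit (the one-sided 80% limit is about 1.10 times the estimate on 52 degrees of freedom, which raises the required n by 1.10² ≈ 1.2), the correlation between baseline and 12 weeks, and completeness;
- the full trial's target difference will be a minimally important difference, agreed with the PPI group and supported by outside evidence;
- the full trial's primary outcome will be chosen on completeness, acceptability and measurement properties, not on the effect observed here;
- between-arm estimates with 95% CIs will be reported as exploratory only.

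With the target fixed this way, the next trial's size no longer depends on the observed effect. For illustration, at 80% power a target of 0.30 SD needs 175 per arm and 0.50 SD needs 63.

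The cost is protocol and analysis-plan wording, with no new data or visits. The downside is that the team can no longer quote a pilot effect size as the basis for the next trial's size.

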### Ethics and dissemination

A favourable ethical opinion for the trial was received from the North of Scotland Research Ethics Committee on 14 April 2025 (REC reference 25/NS/0037) followed by approval from the Health Research Authority (HRA) and Health and Care Research Wales (HCRW) on 25 April 2025. A substantial amendment to the project, which included the addition of a further patient-facing document to be given to participants randomised to the intervention arm, providing local Sparky Samba group details, was approved on 1 July 2025. Any future amendments to the trial protocol will be communicated to individual sites following REC and HRA/HCRW approval. The trial protocol is available via ISRCTN (ISRCTN11861663.)

Results of the trial will be published in the peer-reviewed literature and alongside the trial registration at ISRCTN. A plain language summary of the results will be made available at https://www.cardiff.ac.uk/centre-for-trials-research/research/studies-and-trials/view/Sparky-samba and will also be shared through patient advocacy organisations such as PUK. Additionally, results of the study will be communicated to all participating sites and study participants directly. The design and content of outputs and any additional dissemination will be informed by our PPI steering group.

## Data Availability

Data sharing not applicable as no datasets generated and/or analysed for this study.
